## Abstract

**Background:**

Older adults represent the majority of individuals diagnosed with cancer in the United States and often face complex treatment decisions that require balancing survival benefits with quality-of-life considerations. Despite the emphasis on shared decision-making (SDM), many patients report that clinical guidance does not reflect their personal values. Values-clarification tools have shown slight improvements in aligning care with patient values; however, the factors by which these tools influence decision-making are less studied.

**Objective:**

This pilot study aims to estimate the quality of values-clarification and SDM processes that occur during simulated diagnosis encounters for advanced cancer among participants who do and do not receive a values-clarification tool.

**Methods:**

Pilot randomized study using simulated patient-clinician encounters to assess how values are elicited, processed, and integrated into treatment decisions. Participants aged 60 years and older with an advanced cancer diagnosis will be randomized to receive either a digital values-clarification instrument codeveloped through stakeholder engagement, referred to as Values and Outcomes to Improve Cancer Experiences (VOICE), or a general communication guide from the American Cancer Society (ACS). Each participant will engage in 2 simulated encounters (values-based and nonvalues-based), conducted by trained medical students portraying oncologists. The simulations are structured using a situational awareness framework. A novel rating scale, referred to as VECTORS (Values Elicitation and Clarification of Treatment Options Rating Scale), will measure the quality of rapport building, clinician engagement, and patient engagement through observation. Additional validated instruments will be used to quantify observed (OPTION-5) and patient-reported (CollaboRATE) SDM behaviors and patients’ perceived usefulness of either VOICE or the ACS guide (PrepDM [Preparation for Decision-Making]). Qualitative interviews will be used to better understand participants’ experiences during encounters and perceptions of VOICE or the ACS guide.

**Results:**

The study was conducted between September 2024 and December 2024, with a total of 44 participants, and is ready for data analysis.

**Conclusions:**

This pilot study will provide preliminary evidence into the quality of values-clarification processes occurring during patient-clinician encounters among older adults making treatment decisions for advanced cancer.

**International Registered Report Identifier (IRRID):**

DERR1-10.2196/80531

## Introduction

In 2025, over 2 million people in the United States are expected to be diagnosed with cancer [1], with older adults (aged ≥60 years) comprising the majority of these diagnoses [2]. While cancer is the leading cause of death for older adults [1], their survival rates are improving, making up 78% of the more than 18 million people living with cancer [3]. These advances are positive, but also introduce greater complexity into decision-making [4], as older adults must weigh the benefits of survival to the risks to their quality of life [5]. For those with advanced cancers [6], particularly older adults with comorbidities, treatment pathways can vary and are often influenced by personal values [6,7].

Many older adults report that the guidance they receive from their clinicians does not align with their values when making a treatment decision [8-14]. Patient “values” are the unique preferences, concerns, and expectations a patient brings to a clinical encounter, which should be integrated into clinical decisions for effective patient care [12]. When patients do not engage in values-based communication with their clinicians, it can lead to decisions that negatively impact their quality of life [15], including undergoing aggressive treatments due to patients’ unrealistic expectations of a cure [12,16,17].

Shared decision-making (SDM) guidelines advocate for aligning treatment plans with patient values [14,18-22], and values-clarification tools have shown slight improvements in values-discordance [20]. Research has often focused on decision-making outcomes rather than the process itself, leaving the values-clarification processes that occur during clinical encounters understudied [23,24]. Therefore, to advance knowledge of how patients’ values are discussed, understood, and incorporated into the treatment decision, we applied a situational awareness framework. Situational awareness characterizes an individual’s ability to gather information, comprehend information, and anticipate what will occur after making a decision based on that information [25]. Situational awareness can be assessed using simulations and has been used in health care to identify communication gaps and training opportunities [26-29]. Therefore, applying the situational awareness framework to values-clarification and SDM provides a structured approach to evaluate engagement quality, highlight missed communication opportunities, and conceptualize values-discordance as a potential safety risk given its link to higher treatment burden [21] and more aggressive care [18,22].

This protocol describes a pilot study to estimate the quality of values-clarification and SDM processes during simulated diagnosis encounters for older adults (aged ≥60 years) with advanced cancer, among participants who do and do not receive a values-clarification tool. Using a situational awareness framework, we aim to evaluate how these processes unfold, where they can be strengthened, and how a values-clarification tool may influence engagement. These aims guide the following primary research questions: (1) Do participants in the intervention group experience higher quality values-clarification processes compared to the control group, as measured by a standardized rating scale? (2) Does participant use of the intervention tool influence clinician engagement in values-clarification processes, as measured by a standardized rating scale? (3) Are participants in the intervention group more likely than the control group to initiate discussions about their values during simulated encounters? (4) Does participant initiation of values (compared to clinician initiation) have an impact on the quality of values-clarification processes, as measured by a standardized rating scale?

These aims also guide the following secondary research questions: (1) Does the intervention improve both observed and patient-reported SDM experiences and perceived preparedness for decision-making, compared to the control group? (2) What themes emerge from qualitative data regarding patients’ experiences of value-clarification and decision-making processes during simulated encounters?

## Methods

### Prior Work

We previously developed the Values and Outcomes to Improve Cancer Experiences (VOICE) tool, a digital values-clarification instrument intended to support SDM in oncology settings. To inform the development of VOICE, we conducted a stakeholder-driven concept mapping study involving 7 older adults with advanced cancer, 2 caregivers, and 12 oncology specialists [30,31]. VOICE uses best-worst scaling (BWS) to elicit and prioritize treatment values (ie, what patients value most when making treatment decisions). VOICE also generates a tailored summary report that includes question prompt lists aligned with each patient’s top-ranked treatment values [30,31]. The tailored summary report was designed to prompt patients to discuss their values, ask questions, and express in their own words how the treatment options may affect what matters most to them.

### Study Design

We will conduct a double-blinded randomized pilot study using 2 types of simulated patient-clinician encounters (values-based [VB] and nonvalues-based [NVB]) between an intervention group that will receive VOICE and a control group that will receive an American Cancer Society (ACS) communication guide. Participants randomized to VOICE will complete a series of 7 BWS questions, then receive a tailored summary report based on their values, within Qualtrics. Completing VOICE typically takes up to 8 minutes. See Multimedia Appendix 1 for an example of the BWS instrument and tailored summary report. For this study, we selected the ACS guide as the control condition. Participants randomized to the control group will receive the ACS guide in Qualtrics and typically takes up to 5 minutes to review. The ACS guide was developed as a tool to improve patient-clinician communication and includes a general list of cancer-related question prompts. By comparing VOICE to the ACS guide, we aim to isolate whether tailored summary reports that are aligned with patient values better prepare patients to engage in values-based discussions with their clinicians. Therefore, if VOICE effectively prepares patients, it may prompt clinicians to engage in values-based discussions, subsequently influencing clinician behavior. This conditional structure is embedded in the nonvalues-based simulation script design (see the Simulation Scripts section). The study design schema is described and depicted in Figure 1.

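### Comparing VOICE with the ACS guide estimates the effect of the whole VOICE package; it cannot isolate the tailored summary report, as Study Design says it aims to do

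*Protocol article*

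**What the plan says.** The Study Design section of the protocol article explains the choice of comparator: "we aim to isolate whether tailored summary reports that are aligned with patient values better prepare patients".

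The same section describes the intervention arm: "Participants randomized to VOICE will complete a series of 7 BWS questions, then receive a tailored summary report based on their values, within Qualtrics". The control arm receives the ACS guide in Qualtrics. The article describes this as a communication aid with general cancer-related question prompts, and mentions no values-ranking task for that arm.

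Prior Work describes the two parts of VOICE separately. On the exercise: "VOICE uses best-worst scaling (BWS) to elicit and prioritize treatment values". On the report: "VOICE also generates a tailored summary report that includes question prompt lists aligned with each patient’s top-ranked treatment values".

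The Introduction sets a wider target. The pilot is to estimate the quality of values clarification and shared decision-making "among participants who do and do not receive a values-clarification tool". The research questions that follow compare intervention with control, or ask about the intervention tool; none asks about the report as a separate component.

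**The concern.** The rationale sentence claims a property that the comparison lacks. To isolate the report, the arms would have to differ in the report and in nothing else that could affect the outcome. Here they also differ in whether the participant has just worked through a structured ranking of treatment values.

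That exercise is not a neutral delivery step. By the article's own account it elicits and prioritises values. The primary outcome is the quality of values clarification in the encounter, scored with VECTORS, and one primary research question asks whether participants are more likely to raise their values themselves. Someone who has just ranked what matters most could plausibly raise it without any report, so the extra component bears directly on the outcomes of interest.

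At stake is interpretation. The pilot's stated purpose is to gather preliminary data for a larger study. If a difference were read through the rationale sentence, it would be credited to the report, and a later study might keep or test that component on evidence that does not single it out.

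**Working it through.** The article gives no figure to reproduce, and no sample-size or error-rate calculation applies. The check is whether the between-group contrast identifies the quantity named in the rationale sentence.

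**Step 1: list what each arm receives (Study Design, Prior Work).**

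| Component | VOICE arm | ACS arm |
|---|---|---|
| Values-ranking exercise | 7 BWS questions | none described |
| Question prompts | tailored to top-ranked values | general list |

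Two components differ.

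**Step 2: write down the contrast.** Let Y(e, p) be the mean outcome with the exercise (e = 1) or without it (e = 0), and with tailored prompts (p = 1) or general prompts (p = 0). Define

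- B = Y(1,0) − Y(0,0), the exercise alone;
- R = Y(0,1) − Y(0,0), tailored against general prompts;
- I = the interaction of the two.

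The VOICE arm observes Y(1,1) and the ACS arm observes Y(0,0), so

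VOICE − ACS = Y(1,1) − Y(0,0) = B + R + I.

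**Step 3: when does this equal the report effect?** It equals R only if B + I = 0, that is, if the exercise has no net effect, alone or through interaction with the report. Because the report is built from the rankings, one might instead define the report effect among people who have done the exercise: Y(1,1) − Y(1,0) = R + I. The contrast then equals the report effect only if B = 0. Under either definition an assumption about the exercise is needed, and the article states none.

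**Step 4: look for anything else that separates the components.**

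- *Arms.* Separating them under the second definition needs Y(1,0): participants who complete the BWS exercise and then receive the general guide. No such arm is described.
- *Encounter type.* Every participant has both a values-based and a nonvalues-based encounter. This varies the clinician's script and leaves the make-up of VOICE unchanged.
- *Models.* The generalized estimating equation models estimate differences by group and encounter type, and their interaction. None has a term for a component of VOICE.
- *Performance actions.* Whether a participant brought the report or guide is behaviour after assignment, so comparing those who did with those who did not would not give a component effect.
- *PrepDM and interviews.* Both ask about VOICE or the ACS guide as the tool received. The interviews may suggest which part participants used, but only descriptively.

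Nothing described in the article identifies R or R + I separately from B. A statistical analysis plan could not repair this, because the needed comparison group was not formed.

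**The case against.** The strongest reply is that this is one sentence of rationale, worded as an aim, and that nothing else depends on it. The objective, the primary and secondary research questions, the primary measure and the models are framed as intervention against control, or as VOICE against the ACS guide. The next sentence in Study Design already returns to VOICE as a whole. The sentence can also be read as explaining why a guide containing question prompts was chosen as an active comparator: tailored prompts against general ones. Tailoring needs some elicitation step, and leaving out a third arm is a reasonable scope choice in an unpowered pilot of 44 people.

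Most of this stands, and it limits the point to the one sentence. It does not rescue that sentence. The need for elicitation explains why the exercise accompanies the report; it does not show that the exercise has no effect of its own. An aim that the design cannot meet should not remain as the stated reason for the comparator.

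A reader might infer more than the article supports, in three ways.

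- *That exposure time is a further component, with VOICE 60% longer (8/5 = 1.6).* The article says "Completing VOICE typically takes up to 8 minutes" and gives up to 5 minutes for the guide. Both are typical upper limits, and their ratio does not bound the ratio of actual times. The VOICE time also includes the BWS questions, so it is not an independent difference.
- *That the report's share of any effect lies between 0% and 100%.* The share is R/(B + R + I). If components oppose each other or interact, it can be negative or exceed 100%.
- *That the article's conclusions are wrong.* The Abstract's conclusion and the closing Conclusions speak of values-clarification processes and tools. Neither credits the report alone.

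**Conclusion.** The point holds as a correction to one sentence. The comparison estimates the effect of the VOICE package (BWS exercise plus tailored report) against a general communication guide. It does not isolate the tailored report, because at least two components differ and there is one between-group contrast. The size of the resulting misattribution cannot be stated: the report effect is unidentified without an assumption that B + I = 0 (or B = 0, if the report effect is defined among those who did the exercise).

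This rests on reading the control arm as having no ranking task, which is how the article describes it. It does not require the exercise to have an effect; it is enough that the article gives no reason to assume it has none. The package-level research questions remain answerable as posed, and no estimate, test or sample-size figure changes.

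**What to change.** Replace the rationale sentence in Study Design with a statement that:

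1. the comparison estimates the effect of VOICE as a whole (BWS exercise plus tailored summary report) against a general communication guide;
2. the effects of the separate components are not identified by this design;
3. any difference will not be attributed to the tailored report alone when results are interpreted or used to design the larger study.

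The post-simulation interviews can still be used descriptively to explore which part of VOICE participants drew on. If the report itself is of interest, the larger study could include a comparator that completes the BWS exercise and then receives the general guide.

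The article reports that the study has been conducted and the data are ready for analysis, so the wording can still be settled before results are interpreted. Conduct, sample and analysis do not change. The cost is a narrower claim.

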**Figure 1 figure1:**
[figure not shown]
Randomized pilot testing study schema. (A) Participants will complete informed consent in REDCap (Research Electronic Data Capture) and participant characteristics in Qualtrics remotely before scheduling to engage in simulations. (B) To ensure balanced participation across the 4 potential pathways, a systematic alternating method in Qualtrics will be used to assign participants to the intervention (VOICE) or control (ACS) groups. (C) After participants complete and review VOICE or the ACS guide, they are prompted to contact the research team to schedule the patient-clinician simulated encounters. Patients are reminded they are preparing for a simulated patient-clinician encounter in which they will be asked to discuss and make a decision regarding a “mock” secondary cancer diagnosis. (D) The order of encounter type (VB vs NVB) will be random using a random number generator in Microsoft Excel. (E) All participants will engage in two (20- to 30-minute) simulated encounters (VB and NVB) in random order, both occurring on the same day. Clinicians (ie, medical students portraying oncologists) will only be blinded as to whether the participants received VOICE or the ACS guide prior to the interaction. Clinicians will be informed of the encounter type to ensure they follow appropriate scripts. Simulated encounters will be held at a single site in the Simulation, Experiential Learning, and Training (SET) Center located at the University of North Carolina at Chapel Hill School of Medicine. Simulated patient-clinician encounters will be audio-video recorded. (F) Participants will complete surveys (CollaboRATE and PrepDM [Preparation for Decision-Making]) and engage in semistructured interviews immediately following each simulation. Our research team will complete observed ratings of encounters (VECTORS and OPTION-5) after simulations have concluded by reviewing the audio-recorded simulations. ACS: American Cancer Society; VECTORS: Values Elicitation and Clarification of Treatment Options Rating Scale; VOICE: Values and Outcomes to Improve Cancer Experiences.

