### Data Collection

All data will be collected electronically, deidentified, and stored on a secure HIPAA-compliant drive. Only study team members will have access to these data to maintain confidentiality of study participants. Missing or incomplete data will not be imputed or otherwise adjusted; analyses will be conducted using available data only.

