#### Sample Size and Power

This pilot study was not powered, as its primary objective was to gather preliminary data necessary to inform the design and power calculations of a future, larger-scale study. We aimed to estimate the quality of values-clarification processes during simulated encounters (as measured by VECTORS, ranging from 0 to 100) for intervention and control groups in 2 different simulated encounters (VB and NVB). We will attempt to enroll 11 participants in each pathway to gather preliminary data, for a total of 44 participants.

The preliminary data gathered from this pilot study, as well as other study outcome measures, will inform future work using VECTORS in real-world and simulated encounters.

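### VOICE versus ACS is called randomized, but the only assignment method stated is systematic alternation, and alternating the tool does not by itself balance the four pathways

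*Protocol article*

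**What the plan says.** The Study Design section states: "We will conduct a double-blinded randomized pilot study using 2 types of simulated patient-clinician encounters". It then uses the same term for the arms, as in "Participants randomized to VOICE will complete a series of 7 BWS questions", and again for the control group. The title of Figure 1 also labels the schema randomized. In the Discussion, under Strengths and Limitations, randomization of the tool received is listed among the means by which confounding is controlled.

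The mechanism appears once, in step B of the Figure 1 legend: "To ensure balanced participation across the 4 potential pathways, a systematic alternating method in Qualtrics will be used to assign participants". The groups named there are VOICE and ACS, and the purpose given is balance across four pathways.

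Encounter order is a later, separate step (D): "The order of encounter type (VB vs NVB) will be random using a random number generator in Microsoft Excel". The article does not say whether that draw was restricted, either overall or within arm.

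Sample Size and Power gives the target: "We will attempt to enroll 11 participants in each pathway to gather preliminary data, for a total of 44 participants". The Results section reports 44 participants, ready for analysis, without counts per pathway.

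**The concern.** There are two separate problems.

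First, the design label and the stated mechanism disagree on the main comparison. Alternation contains no random element: given one assignment and the sequence, the next is determined. Primary research questions 1 to 3 in the Introduction all compare VOICE with ACS or ask what the tool does, so they draw on a property that the described assignment lacks. The Discussion's statement on confounding relies on the same property.

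Second, the stated purpose does not follow from the method. Alternating the tool equalizes VOICE and ACS. It does nothing about which encounter comes first, which is the other factor needed to make four pathways. If order is uneven between arms and there is any learning or fatigue from the first encounter to the second, that unevenness enters the contrast of VB minus NVB between arms. This is the interaction that the generalized estimating equation (GEE) models are meant to test.

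**Working it through.** **Label against mechanism.** No arithmetic applies. Study Design, the Figure 1 title and Strengths and Limitations say randomized; Figure 1 step B says alternated. A random generator is named only for order (step D). If Qualtrics in fact used a random element, step B is wrong. If it did not, the other three places are wrong. Some text must change in either case.

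**The plan's own figure.** 4 pathways × 11 = 44, which reproduces. Everyone does both encounter types, so the reading of the pathways that fits is arm (2) × order (2). This is an inference, because the figure itself is not shown.

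**Pathway balance.** Assumptions: alternation gives exactly 22 per arm, and nobody is lost before the simulations.

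- *Order drawn 1:1 without restriction.* The number doing VB first in an arm is Bin(22, 0.5), with SD √(22 × 0.25) = 2.35.
  - P(exactly 11 in one arm) = C(22,11)/2^22 = 0.168.
  - P(exactly 11 in all four) = 0.168² = 0.028.
  - P(all four between 9 and 13) = 0.714² = 0.51.
- *Order list fixed at 22/22 overall, not by arm.* P(exactly 11 in all four) = C(22,11)²/C(44,22) = 0.237.
- *Order blocked within arm.* The probability is 1.

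**What order imbalance does.** Suppose the second encounter scores δ outcome SD higher or lower than the first, whichever type it is. Let p be the share of an arm doing VB first.

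- The average of a participant's two encounters always contains one first and one second encounter, so δ cancels from the arm main effect when both are observed.
- The mean VB-minus-NVB difference in an arm is shifted by δ(1 − 2p). The interaction is therefore shifted by 2δ times the arm difference in p.
- With unrestricted draws, the SD of the arm difference in p is √(2 × 0.25/22) = 0.151, and its mean is zero.
- The documents give no δ. Assuming 0.2, the error SD is 2 × 0.2 × 0.151 = 0.06. Assuming 0.5, it is 2 × 0.5 × 0.151 = 0.15.

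**Scale.** At an assumed within-person correlation of 0.5, the interaction's standard error is √(4 × 0.5/22) = 0.30 outcome SD (0.23 at correlation 0.7, 0.36 at 0.3). Adding 0.15 in quadrature gives √(0.30² + 0.15²) = 0.34.

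**The case against.** The defence has several good points.

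- *Order is random.* It would be wrong to conclude that the study has no randomized element. Only the assignment to VOICE or ACS lacks one.
- *The target is an attempt.* Eleven per pathway is worded as an aim, and an article may leave any restriction of the Excel draw to a fuller document. A reader might take 0.028 as showing that balance failed. It does not: that figure belongs to one of three possible procedures, and the achieved counts are not reported. What stands is that alternating the tool cannot by itself secure balance across four pathways.
- *Foreseeability is not shown.* A reader might infer that staff steered enrolment. The lettered steps put consent in REDCap and the remote Qualtrics questionnaire before Qualtrics assigns the tool. Staff would have to know the last assignment and control who comes next, and the article describes no such access. Concealment is not described either, so selection remains a risk and no more.
- *Attrition is a different matter.* The legend says: "After participants complete and review VOICE or the ACS guide, they are prompted to contact the research team to schedule". Together with "Missing or incomplete data will not be imputed or otherwise adjusted; analyses will be conducted using available data only", this means that people who stop after seeing a tool contribute no outcome data. That would be equally true under perfect randomization, and no such loss is reported. It is a reason to report the flow of participants, but it is not a consequence of alternation.
- *The order error is imprecision.* It has mean zero, depends on an assumed δ, and is modest beside the interaction's own standard error in an unpowered pilot.

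None of this removes the contradiction between the randomized label and the alternating mechanism.

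**Conclusion.** The point holds in a limited form. As described, VOICE versus ACS is a quasi-randomized comparison reported under a randomized label, and the claim that randomization controls confounding between tools is not supported by the stated method. This rests on the text alone and needs no assumption.

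The balance claim is unsupported as worded. How unlikely exact balance was depends on an unreported detail: 0.028, 0.237 or 1 for unrestricted, overall-fixed or within-arm-blocked order, given the arm-by-order reading, 22 per arm and no losses.

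The effect of order imbalance is confined to chance error in the interaction, with SD about 0.06 to 0.15 outcome SD for assumed order effects of 0.2 to 0.5 SD and unrestricted draws. The documents do not support saying that order biases the arm main effect, that enrolment was manipulated, or that one arm lost more participants.

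**What to change.** Data collection is finished but the article reports the data only as ready for analysis, so these changes are still timely.

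1. State how Qualtrics actually assigned the tool and who could see the assignments. If it was alternation, call the arm assignment quasi-randomized in Study Design and in the Figure 1 title and legend.
2. Qualify the confounding statement in Strengths and Limitations, and limit causal wording for VOICE versus ACS.
3. State whether the order draw was restricted. Replace the claim that alternation ensures balance with the balance achieved.
4. Report the numbers assigned and attended in each of the four pathways, with baseline characteristics by arm.
5. Add encounter order to the GEE models, with one or two baseline covariates named before analysis and confirmed to have been collected before tool exposure. Preferred role in problem-solving and decision-making (PSDM) is a candidate. The Self-Reflection and Insight Scale is doubtful, because Participant Characteristics also describes it as reflecting perceptions of the tool.

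For the larger study, one concealed, restricted random list over the four tool-by-order pathways would settle both problems.

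The cost is a less favourable design label, a count table from study records and a few degrees of freedom. No further participants are needed. Adjustment can reduce measured imbalance, but it does not turn alternation into randomization.
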